**Primary question:**

What is the effect of adding educational outreach (AF+EO) compared to the ‘usual’ offering of audit and feedback (AF) and communities of practices on:

1. The prescribing of antipsychotic medications in LTC
2. The rate of falls in LTC

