### **Data collection**

Outcomes will be assessed using population-level administrative databases linked through unique, encrypted patient identifiers at the Institute for Clinical Evaluative Sciences (ICES). Data will be compiled from the following databases: 1) the Ontario Drug Benefits (ODB) database, covering all prescription medications dispensed to residents in long-term care homes; 2) the Canadian Institute for Health Information (CIHI) databases covering all hospitalizations and emergency department visits; 3) the Ontario Health Insurance Plan (OHIP) database, covering physician billings for procedures and

consultations; 4) the Registered Persons Database covering demographic information including date of death; and 5) the Continuing Care Reporting System (CCRS) database for clinical and demographic information on LTC residents collected using the Resident Assessment Instrument (RAI). Each LTC resident in the province receives a ‘full’ RAI assessment within 2 weeks from admission date, every 12 months from previous full assessment or any other time when the clinical condition of a patient changed considerably and each resident also receives a ‘quarterly’ assessment every 3 months. For each resident, the CCRS database holds demographic and clinical information, including data regarding clinical diagnoses (e.g., dementia, psychosis), dispensing of antipsychotic medications, and occurrences of falls. In addition, a number of validated outcome scales can be derived from the CCRS data, including those related to ADLs, aggressive behaviour, pain, and mood.

The process evaluation involves a mixed-methods approach using individual qualitative interviews and quantitative prescriber surveys.

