### **Outcomes**

The following primary and secondary prescribing and clinical outcomes will be assessed in the trial:

| Variable        | Definition | Source |
|-----------------|------------|--------|
| Primary outcome |            |        |

|                                                   |                                                                                       |                   |
|---------------------------------------------------|---------------------------------------------------------------------------------------|-------------------|
| Antipsychotic dispensing                          | Number of days with antipsychotic prescriptions in the last week (count, range 0 – 7) | RAI               |
| Secondary prescribing outcomes             |                                                                                       |                   |
| Antipsychotic prescribing                         | Any antipsychotic Rx during the past month (dichotomous)                              | ODB               |
| Mean Antipsychotic dose                           | Dose equivalent of antipsychotic dispensed in the past month (continuous)             | ODB               |
| Benzodiazepine (or z-drug) prescribing            | Any Rx during the past month (dichotomous)                                            | ODB               |
| Anti-depressant prescribing                       | Any Rx during the past month (dichotomous)                                            | ODB               |
| Acetaminophen prescribing                         | Any Rx during the past month (dichotomous)                                            | ODB               |
| Secondary clinical outcomes                |                                                                                       |                   |
| Difficulty in performing activities               | ADL long form scale (continuous variable, range 0-28)                                 | RAI (ADL_long_cc) |
| Aggressive behaviour scale                        | Extent of aggressive behaviour (continuous variable, range 0-12)                      | RAI (ABS_cc)      |
| Pain                                              | Pain scale (continuous variable, range 0-3)                                           | RAI (PAIN_cc)     |

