### **Analysis**

Descriptive statistics will be calculated for all variables of interest: continuous variables with a normal distribution will be described using means and standard deviations (medians and inter-quartile ranges in the case of skewed distributions), whereas categorical variables will be summarized using frequencies and proportions. All analyses will be by Intention To Treat. Analyses will be conducted using SAS v.9.3 and statistical significance will be assessed at the 5% level.

The **primary outcome** describing **dispensing of medication** (number of days with antipsychotic/benzodiazepine/antihypertensive/anticholinergic prescriptions in the last week) will be analyzed using generalized linear mixed effects regression with multinomial distribution and cumulative logit link. To account for the staggered implementation of the intervention, phase (phase1/phase2) will be included as a fixed effect. Random intercepts and slopes will be specified to account for intracluster

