and inter-period correlations. To maximize statistical efficiency, the analysis of prescribing outcomes will adjust for the stratification factors as well as public/private home ownership and the following patient covariates: age, sex, levels of function and aggressive behaviour (using multiple imputation for missing covariates if necessary). The effect of the intervention at 6 months will be expressed as cumulative Odds Ratio (OR) with 95% confidence interval (CI). In case of non-convergence or violation of the proportional odds assumption using the score test, the normal distribution and identity link will be used. The dichotomous **prescribing** outcomes (i.e., any relevant prescription in the last month) at baseline, 3 months, and 6 months will be analyzed using generalized linear mixed effects regression with binomial distribution and logit link function. Fixed and random effects will be specified as described for the primary outcome. The fixed effects of time, intervention, and intervention by time will be the main variables of interest. Dose equivalent of antipsychotic dispensed in the past month at baseline, 3 months, and 6 months will be analyzed using linear mixed effects regression with normal distribution and identity link. Fixed and random effects will be specified as described for the primary outcome. The effect of the intervention will be described as difference in change from baseline to 6 months using adjusted least square means with 95% CI. In the case of substantial skewness, gamma distribution with log link or log-normal distribution will be considered, and difference in change from baseline will be expressed as adjusted relative mean difference with 95% CI.

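### The primary outcome is antipsychotic days in the outcome table, four drug classes in the analysis section, and has falls beside it in the primary question

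*Protocol*

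**What the plan says.** Four parts of the Protocol bear on what is primary.

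- **Primary question.** There are two numbered items: "The prescribing of antipsychotic medications in LTC" and "The rate of falls in LTC".
- **Outcomes table.** There is one primary row: "Number of days with antipsychotic prescriptions in the last week", scored 0 to 7 and taken from the RAI. Falls is a secondary clinical outcome, as a past-month count. Benzodiazepine prescribing is a secondary past-month yes/no outcome from ODB. Antihypertensives and anticholinergics have no row.
- **Analysis.** The primary dispensing outcome is "number of days with antipsychotic/benzodiazepine/antihypertensive/anticholinergic prescriptions in the last week", analysed with a cumulative logit mixed model and reported as an odds ratio at 6 months. Falls appears among the secondary clinical outcomes, now as any fall versus none. The only statement on error rates is that "statistical significance will be assessed at the 5% level".
- **Power.** The ordinal primary outcome is antipsychotic days only. No power is given for falls or for the other three classes.

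The secondary questions also place the three added classes. All three are examples of drugs that raise fall risk (item iv), and benzodiazepines are also an example of a possible alternative to antipsychotics (item iii).

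**The concern.** The primary outcome decides whether the trial is called positive. Here the reader can choose among several, each with some support in the text. If antipsychotic days showed no effect, a significant result on benzodiazepines, antihypertensives, anticholinergics or falls could still be presented as primary. The Implementation timetable links a later launch of educational outreach in control homes to approval of scale-up, so the choice has consequences.

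Interpretation suffers too. A rise in benzodiazepines could be substitution for antipsychotics (item iii), and a drop could be a gain on fall risk (item iv). The favourable direction is therefore not fixed for that class. If the slash list is a single composite, substitution could mask a real antipsychotic effect, and the composite would not be the outcome that was powered.

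**Working it through.** **Step 1. The sections side by side.**

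| Item | Primary question | Outcomes table | Analysis | Power |
|---|---|---|---|---|
| Antipsychotics | Primary | Primary, days in week | Primary, days in week | Primary, days in week |
| Benzodiazepines | Not named | Secondary, past-month yes/no | In the primary definition, days in week | Not covered |
| Antihypertensives, anticholinergics | Not named | No row | In the primary definition, days in week | Not covered |
| Falls | Primary, as a rate | Secondary, count | Secondary, any/none | Not covered |

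Only the antipsychotic row is consistent throughout.

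**Step 2. What the slash list can mean.** (a) Four outcomes tested separately; (b) one composite, days with any of the four classes; (c) shorthand for a topic-specific dispensing outcome. The text does not settle which.

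**Step 3. Error rates.** Inputs: level 0.05 per test (Analysis), taken as two-sided because 95% intervals are planned; k tests counted from Step 1. For independent tests the chance of at least one false positive is 1 − 0.95^k. The Protocol's own level is the case k = 1: 1 − 0.95 = 5%.

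- k = 2: 1 − 0.9025 = 9.75%
- k = 4: 1 − 0.8145 = 18.5%
- k = 5: 1 − 0.7738 = 22.6% (the bound without independence is 5 × 5% = 25%)

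The outcomes come from the same homes and residents, so some correlation is likely. The Protocol gives none. Assuming equally correlated normal test statistics, a simulation of 400,000 draws gives:

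| Reading | k | Independent | Correlation 0.3 | 0.5 | 0.8 |
|---|---|---|---|---|---|
| Antipsychotics only | 1 | 5.0% | – | – | – |
| One drug outcome (antipsychotics, composite or topic-specific) plus falls | 2 | 9.75% | 9.6% | 9.0% | 7.8% |
| Four classes separately | 4 | 18.5% | 17.4% | 15.5% | 11.4% |
| Widest reading of every section combined | 5 | 22.6% | 20.9% | 18.2% | 12.8% |

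**Step 4. Cost of splitting the level.** Take the stated 80% power at 5%. At 2.5% per test, power is Φ(1.960 + 0.842 − 2.241) = Φ(0.561), about 71%. The stated 80% itself does not reproduce from its inputs. With 15 and 30 clusters of 120, a design effect of 1 + 119 × 0.01 = 2.19 and 30% versus 20.5%, a two-proportion approximation gives over 99% at either level. That is a separate matter, and this point does not depend on it.

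**Step 5. Timing.** As the Implementation timetable reads in the available text, Phase 1 homes complete six-month follow-up in March–April 2016 and the falls topic starts in May–June 2016. Falls is nevertheless scheduled at 3 and 6 months post-intervention. For Phase 1 homes those readings would precede the falls topic.

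**The case against.** The strongest reply is that the plan has one primary outcome and some loose wording. The table and the power statement agree, the Analysis section speaks of the primary outcome in the singular, and the slash list may be shorthand added when falls became a second topic. Test order and allocation of the level are commonly left to a statistical analysis plan, which is not shown.

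Much of this stands. The absence of a multiplicity rule is not a fault here, and testing each outcome at 5% is inferred from one general sentence. What remains is the contradiction within the Protocol over which outcome is primary.

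Three stronger inferences are tempting and should not be drawn.

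- **Five chances of success.** No section yields five primaries. The primary question gives two and names no other drug class; the Analysis section gives at most four and puts falls among the secondary outcomes; the table and the power statement give one. Five arises only by taking the widest part of each section and ignoring the rest of it.
- **The RAI holds no drug data beyond antipsychotics.** Data collection mentions "dispensing of antipsychotic medications, and occurrences of falls" within a list introduced as inclusive. What can be said is that no outcome row defines weekly days for the other classes.
- **All three added classes belong to the falls topic alone.** Benzodiazepines are also tied to the antipsychotic topic, though as a secondary question.

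**Conclusion.** The point holds as an inconsistency in the definition of the primary outcome and in the status and definition of falls. It needs correcting because the sections conflict on what would count as success. The inflation depends on the reading: 9.75% for antipsychotics plus falls and 18.5% for four separately tested classes, both assuming independence and 5% per test. A reader might infer 22.6%. That is the independent-test figure for a combination no section states, and it drops to about 13% to 21% for five tests equally correlated at an assumed 0.8 to 0.3. If the slash list is a composite and falls is secondary, there is no inflation, but the outcome analysed is not the one that was powered.

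**What to change.** State antipsychotic days in the last week at 6 months as the sole primary outcome for the antipsychotic topic, in the same terms in the primary question, the Outcomes table, Analysis and Power. Delete the other three classes from the primary definition in Analysis and list them as secondary past-month ODB outcomes, adding rows for antihypertensives and anticholinergics.

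For falls, choose one status and one definition (rate, count or any/none) and use them throughout. Two options are open:

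1. Keep falls secondary and correct the primary question. This fits the Outcomes table, the Analysis section and the power statement.
2. Make falls the primary outcome for the falls topic, timed from the introduction of that topic, and test it after antipsychotics in fixed order.

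Fixed order leaves antipsychotics the full 5%. A 2.5% split is possible, but the documents do not require it, and from the stated 80% it would lower power to about 71%.

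The cost is mostly wording. Falls and the other drug classes could no longer be claimed as independent primary successes, and option 2 needs a separate power statement for falls.

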### ***Power***

Our sample size is determined primarily by pragmatic considerations and logistical constraints. A total of **58 LTC homes** will be included in the trial: a maximum of 38 homes allocated to receiving the full intervention and 20 homes to receiving usual care. After grouping homes sharing providers together, we anticipate a total of 45 independent clusters (30 intervention, 15 control). For our primary outcome measured as an **ordinal** variable (number of days with antipsychotic prescription in the past 7 days), 45

homes with 2:1 allocation will yield 80% power to detect a cumulative Odds Ratio (i.e., odds of being in a higher category) of 0.6, assuming an intracluster correlation coefficient (ICC) of 0.01 and an average of 120 residents per home. Assuming that 30% of control arm patients will have 7 days of antipsychotic prescriptions, an OR of 0.6 implies a reduction in this proportion in the intervention arm to 20%.

To ensure we will be able to detect clinically important differences with adequate power for our secondary prescribing outcome (measured as a **dichotomous** variable), we used a simulation study with 1000 simulation runs to determine the required effect size (difference in change from baseline to 6 months in antipsychotic prescribing between the arms) that can be detected with at least 80% power. For this simulation, we assumed a conservative ICC of 0.1, an average of 120 residents per home, and a control arm proportion of 30%. With 45 homes (30 intervention, 15 control), we will have **83.4%** power to detect an OR of approximately 0.75 at 6 months. Assuming a control arm proportion of 30%, this OR corresponds to a reduction in the intervention arm to approximately 25%.

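### A preliminary score test of proportional odds, not restricted to the treatment terms, decides whether the primary result is the cumulative odds ratio or a normal-model result with no stated effect measure, target or power

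*Protocol*

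**What the plan says.** The primary outcome in the Protocol's Outcomes table is "Number of days with antipsychotic prescriptions in the last week (count, range 0 – 7"), an ordinal variable with eight levels and seven cut points. The Analysis section fits a cumulative-logit mixed model. It adjusts for phase, the stratification factors (hub, baseline antipsychotic rate and home size, from the Allocation section), ownership, age, sex, function and aggressive behaviour. It then states: "The effect of the intervention at 6 months will be expressed as cumulative Odds Ratio (OR") with a 95% confidence interval. The next sentence is the switch: "In case of non-convergence or violation of the proportional odds assumption using the score test, the normal distribution and identity link will be used".

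The section does not say which terms the score test covers, at what level beyond the general 5%, or how it allows for the random effects. It names no effect measure for the primary outcome under the fallback and does not say that the OR would still be reported. For the dose outcome, by contrast, the same section names the measure both for the main model (difference in change, from adjusted least square means) and for its fallback (adjusted relative mean difference).

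The Power section states power for the primary outcome on one scale only: 45 homes at 2:1 "will yield 80% power to detect a cumulative Odds Ratio (i.e., odds of being in a higher category) of 0.6".

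**The concern.** A preliminary test on the trial data selects the scale of the headline result. Such a test measures evidence against exact proportionality, not whether a departure matters. With many observations it flags small departures. If it covers all terms, the departure may lie in age or aggressive behaviour and have no bearing on the treatment effect.

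If the switch is triggered, the prespecified and powered OR gives way to a normal-model result, presumably a mean difference in days, for which the protocol sets no target and no power. Which of the two becomes the primary result is then known only after the data have been examined.

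**Working it through.** **Inputs from the Protocol.** Power section: "A total of 58 LTC homes will be included in the trial", "we anticipate a total of 45 independent clusters (30 intervention, 15 control"), "an average of 120 residents per home", ICC 0.01, and 30% of control residents with 7 days. Outcomes section: three measurement times. Analysis section: 5% level.

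**Assumed, because the documents do not give them.** Share of residents with 1 to 6 days (2%, 3% or 6%), covariate slopes, 15 model terms (3 hubs, two-level strata), and a correlation of 0.8 between repeated measures in some runs.

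**The plan's own figures.** OR 0.6 against 30%: odds = 0.6 × 0.30/0.70 = 0.257, so the proportion is 0.257/1.257 = 20.5%, which agrees with the stated 20%. The 80% power does not reproduce. The design effect is 1 + 119 × 0.01 = 2.19, and 3,600 v 1,800 residents at 20.5% v 30% give about 99.9% two-sided. That is a separate matter and does not affect this point.

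**Number of observations.** 58 × 120 × 3 = 20,880. On the 45-home power basis, 45 × 120 × 3 = 16,200. The exclusions and the presence rule lower both.

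**Sensitivity of the test, by hand.** Take two splits, at least 1 day (probability p1) and 7 days (p2), and a covariate scaled to SD 1. Near zero slope, the variance of the difference between the two slopes is

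[1/(p1(1−p1)) + 1/(p2(1−p2)) − 2/(p1(1−p2))] / N.

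- p2 = 0.30, p1 = 0.33, N = 20,880: (4.523 + 4.762 − 8.658)/20,880, so SE = 0.0055. A slope gap of 0.05 is about 9 SE.
- p1 = 0.36: (4.340 + 4.762 − 7.937)/20,880, so SE = 0.0075. The same gap is 6.7 SE.
- p1 = 0.36, N = 16,200: SE = 0.0085. On a joint 15-df test, gaps of 0.01, 0.02 and 0.03 give rejection of about 9%, 25% and 58%.

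**Simulation with all seven cut points.** Global score test over 15 terms, 15 × 6 = 90 df, 50 to 60 runs per setting (Monte Carlo SE up to about 7 points), 6% mid-scale unless stated. The treatment effect is proportional throughout, with true OR 0.60. The test as simulated ignores random effects.

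| Departure | Observations | Rejection |
|---|---|---|
| None, ICC 0 or 0.01 | 20,880 | 3% to 7% |
| None, ICC 0.1 | 20,880 | 8% to 10% |
| One covariate, drift 0.03 | 20,880 | 28% |
| Three covariates, drift 0.03 each | 20,880 | 88% |
| One covariate, drift 0.05 (OR per SD 1.35 to 1.28) | 20,880 | 84% |
| Same, ICC 0.01 and repeated measures | 20,880 | 80% |
| Same, 2% mid-scale | 20,880 | 100% |
| Same, 6% mid-scale | 16,200 | 74% |
| Same, 6% mid-scale | 2,088 | 7% |
| One covariate, drift 0.10 | 16,200 or 20,880 | 100% |

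In the 0.05 setting at 20,880 observations the pooled treatment OR averaged 0.598, so the rejections carried no information about treatment. A test limited to the treatment terms (3 × 6 = 18 df) rejected in 9 of 60 runs (15%) on data of that kind. A separate two-split simulation (45 clusters × 155 residents × 3 times, 150 trials per scenario) gave 99% to 100% for the global test at a gap of 0.05, 4% to 5% for the treatment-by-time term alone, and 3% to 9% for the global test with proportional odds true.

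**After the switch.** If residents sit only at 0 or 7 days, the OR target corresponds to 7 × (0.300 − 0.2045) = 0.67 days. The protocol does not state this or any other target in days.

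**The case against.** The protocol never says that the test is global. Its scope and level could properly be settled in an analysis plan that is not shown, and a test of the treatment terms alone would seldom trigger the switch. This stands: the global reading is an inference. But the switch itself is fixed in the protocol, without that restriction.

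The size of the departure is unknown, and 0.05 is not always trivial. With 3% mid-scale the two splits lie only logit(0.33) − logit(0.30) = 0.139 apart, so a gap of 0.05 per SD would make the cumulative logits cross at 0.139/0.05 = 2.8 SD. This also stands. The near-certain rejection in that setting should not be relied on, and the rates belong in a range that includes 28% at 0.03.

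The rule is prespecified and names its fallback model. If nuisance covariates drive the trigger, it offers no obvious route to a favourable choice, and the target can be converted to days. That is fair, and it limits the harm. It does not remove it: the protocol makes no such conversion and does not keep the OR as a reported result.

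A reader might go further and infer that the cumulative OR would almost never be the primary result, or that the type I error is inflated. The documents support neither. Sample size alone does not cause rejection (3% to 10% when proportional odds holds), and no calculation here shows bias, inflation or loss of power under the normal model.

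**Conclusion.** The point holds as a badly fixed rule. A preliminary test decides whether the primary result is on the scale for which the trial was planned or on one with no stated effect measure, target or power. Nothing limits that test to the terms that matter.

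The chance of a switch cannot be stated as one figure. If the test is global and the departure is confined to one nuisance covariate, it runs from 28% at a drift of 0.03 per SD, through 74% to 84% at 0.05, to 100% at 0.10 (6% mid-scale). It falls to about 3% to 10% under exact proportionality, and to about 4% to 15% if only treatment terms are tested. All of these depend on the assumed slopes and mid-scale share, and on a simulated test that ignores the random effects. The consequence is a data-chosen primary effect scale. It should be corrected, but it does not by itself invalidate the analysis.

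**What to change.** 1. Remove the score test as a switch. State that the cumulative OR at 6 months is the primary effect whatever any test of proportional odds shows.
2. Assess proportionality for the treatment-by-time terms only, and descriptively: report the treatment ORs for any day and for 7 days as supportive results.
3. Give the normal-model mean difference in days as a named sensitivity analysis.
4. Keep one prespecified fallback for non-convergence only, with its effect measure stated. A marginal model with home-clustered standard errors is not a good choice: its OR is a different quantity from the mixed-model OR, and there are only 15 control clusters.

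The cost is a change of wording plus two supportive estimates. The small downside is that under real non-proportionality the single OR averages over the splits, which the supportive ORs make visible.

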#### ***Antipsychotics: evidence of over-use***

Ontario has one of the highest rates in Canada and is known to have one of the highest rates in the world of antipsychotic use. The Canadian Institute for Health Information (2014) reports that 30.5% of LTC residents are inappropriately prescribed antipsychotic medications, without a diagnosis of psychosis. According to a recent report from the Ontario Drug Policy Research Network, in 2012, 38.0% of residents in LTC were dispensed an antipsychotic.

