| Depression                                        | Depression rating scale (continuous variable, range 0-14)                             | RAI (DRS_cc)      |
| Falls                                             | Number of falls in the past month (count)                                             | RAI (J4: a)       |
| Secondary health care utilization outcomes |                                                                                       |                   |
| ER visits                                         | Number of ER visits during the previous 6 months (count)                              | CIHI/NACRS        |
| Hospitalizations                                  | Number of hospital visits visit during the previous 6 months (count)                  | CIHI              |

All **primary and secondary prescribing outcomes** will be assessed at baseline (pre-intervention) and at 3 and 6 months post-intervention. Here, "baseline" is defined as the week or month immediately prior to randomization, while post-intervention measurements are defined as the third and sixth months after randomization. These outcomes will be assessed on all residents who are alive at the time of the assessment and who were present in the home for the full duration of the prior week/month.

All **clinical outcomes** (e.g., ADL, behaviour scale, depression, falls) will be assessed at baseline and at 3 and 6 months post-intervention. The most current data collected immediately prior to the implementation of the intervention, and at each post-randomization time point will be used, regardless of mortality status at the subsequent time point.

All **health care utilization outcomes** (number of ER visits and hospitalizations during the previous 6 months) will be assessed at baseline and at 6 months post-intervention. A longer duration is required to allow adequate time for the intervention to have an effect on these outcomes. All residents present in the homes at any time during the study will contribute to the analysis using person-time of follow-up. As the EO intervention may be rolled out over a 2-3 month period due to logistical restraints, homes allocated to the control arm will have their measurement times assigned randomly from the assessment times of the intervention homes in the same stratum.

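### The gamma or log-normal fallback for antipsychotic dose cannot be fitted to all residents, because roughly 62–70% of them would have a dose of zero

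*Protocol*

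**What the plan says.** The Outcomes table lists mean antipsychotic dose as a secondary prescribing outcome, taken from the drug benefit database and defined as "Dose equivalent of antipsychotic dispensed in the past month (continuous"). The row does not restrict it to users. The text below the table fixes the population for all primary and secondary prescribing outcomes: "These outcomes will be assessed on all residents who are alive at the time of the assessment", provided they were in the home for the whole of the preceding week or month. The Analysis section declares every analysis to be by intention to treat.

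For dose, the Analysis section's first choice is a linear mixed model with normal errors and identity link, which accepts zeros. It then adds: "In the case of substantial skewness, gamma distribution with log link or log-normal distribution will be considered", and in that event "difference in change from baseline will be expressed as adjusted relative mean difference with 95% CI". It does not define substantial skewness. It gives no rule for residents with no antipsychotic dispensed: no two-part or zero-tolerant model, no added constant and no declared users-only estimand.

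On use rates, the background section reports that "in 2012, 38.0% of residents in LTC were dispensed an antipsychotic", and the simulation in the Power section assumes "a control arm proportion of 30" per cent.

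**The concern.** A resident with nothing dispensed in the month has a dose of zero, and on the protocol's figures that is most residents. A gamma or log-normal likelihood cannot use those records, so the named alternative does not fit the named population.

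The probable practical outcome is that the zeros are dropped and users are compared with users. Whether a resident is a user at 6 months is something outreach aims to change, so the contrast is no longer between randomised groups. The effect is also a difference in change from baseline, so each time point would draw on a different selected subset. A real fall in dose per resident could then appear smaller, vanish or change sign. Adding a small constant to rescue the zeros is not in the protocol either, and would let an arbitrary number set the size of the ratio.

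**Working it through.** **Inputs from the protocol.** Use 38.0% and 30.5% (background); 30% control and about 25% intervention, odds ratio 0.75, 120 residents per home, 30 and 15 clusters (Power). The protocol gives no dose distribution, so every dose below is an assumption.

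**1. Reproduce the plan's intervention-arm proportion.** Control odds 0.30/0.70 = 0.4286; times 0.75 = 0.3214; 0.3214/1.3214 = 24.3%. The plan says approximately 25%, so it reproduces.

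**2. Share of zeros = 1 − users.** 1 − 0.38 = 62.0%; 1 − 0.305 = 69.5%; 1 − 0.30 = 70%. In the intervention arm at the planned effect, 1 − 0.25 = about 75%.

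**3. Can zero be fitted?** At dose 0 the log-normal log-density is −∞. The gamma log-density is −∞ (shape 1.5) or +∞ (shape 0.5). Zeros cannot enter either likelihood.

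**4. How likely is the trigger?** If all users took the same dose, skewness would be (1 − 2p)/√(p(1 − p)): 0.49 at p = 0.38, 0.87 at p = 0.30, 1.15 at p = 0.25. Variation in dose among users adds to this. With log-normal user doses and an assumed coefficient of variation of 0.8, pooled skewness was about 3.5–3.8. The trigger is likely, but not certain.

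**5. Size of the distortion.** Users-only ratio = all-resident ratio × (control use ÷ intervention use). With 30% v 25% users the multiplier is 0.30/0.25 = 1.2. Baselines are taken as equal and continuing users' doses as unchanged.

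- *High-dose users stop.* Half of users at 100 units, half at 25; 5 points of the high group stop. Control 0.15×25 + 0.15×100 = 18.75; intervention 0.15×25 + 0.10×100 = 13.75. All residents: 13.75/18.75 = 0.73. Users: 55.0/62.5 = 0.88.
- *Stopping unrelated to dose.* All residents: 0.25/0.30 = 0.83. Users: 1.00.
- *Low-dose users stop.* Stoppers at half the average dose. All residents: (0.30 − 0.05×0.5)/0.30 = 0.275/0.30, a fall of 8.3%. Users: 0.275/0.25 = 1.10, a rise of 10.0%.

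Variants of the last case:

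| Users | Points stopped | Stoppers' dose v average | Per resident | Per user |
|---|---|---|---|---|
| 30% | 5 | 33% | −5.5% | +13.4% |
| 30% | 5 | 80% | −13.3% | +4.0% |
| 38% | 6 | 50% | −7.9% | +9.4% |

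**6. Simulation check.** 1,800 control and 3,600 intervention residents, 30% users, log-normal doses as in step 4, one sixth of users stopped; clustering was ignored, as only the means matter here. Stopping weighted to low doses: 0.87–0.90 for all residents v 1.04–1.08 for users. Unrelated to dose: 0.83 v 1.00. Weighted to high doses: 0.74–0.79 v 0.88–0.94.

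**7. Adding a constant.** In one simulated data set with stopping weighted to low doses, where users average 1 unit in control, the log-normal ratio was 0.69, 0.78, 0.89 and 0.97 for constants of 0.001, 0.01, 0.1 and 1.

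**The case against.** The fallback is only to be considered. The planned model accepts zeros, nothing says that they will be discarded, and the treatment of zeros in a conditional option for one secondary outcome might be left to a statistical analysis plan. This stands as a limit on certainty, but it does not remove the point: the protocol itself names two distributions that its own population rules out, and names no other.

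A reader might infer more than the documents support:

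- *That the skewness trigger is met by construction.* The protocol sets no threshold, and zeros alone give a skewness of only 0.49–0.87 at 38–30% users.
- *That a successful intervention would be reported as a dose increase.* Reversal needs stoppers with below-average doses and little dose reduction among those who continue. In the +10.0% example, a 9.1% cut among continuing users cancels it (1.10 × 0.909 = 1.00), and dose cutting is part of what this outcome measures.
- *That gamma and log-normal must be struck out altogether.* Either can serve as the positive part of a two-part model.

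The row label could be read as mean dose among those dispensed a drug. The population sentence in the Outcomes section says otherwise, and on that reading the first-choice linear model would have the same selection problem.

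The zero share is approximate. The 38.0% is a 2012 figure with no stated monthly window, and the 30% is a planning assumption. Preferential recruitment of high-rate homes would lower the share of zeros; excluding residents with schizophrenia or bipolar disorder would raise it.

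**Conclusion.** The point holds as a mismatch between a named method and the stated population. With roughly 62–70% zeros, the stand-alone gamma or log-normal model cannot be fitted to all residents. The skewness that would invoke it is likely, and a users-only comparison is the probable, though not the stated, result. That comparison conditions on post-randomisation use and departs from intention to treat.

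The direction and size of the distortion depend on who stops: attenuation (0.73 to 0.88), disappearance (0.83 to 1.00) or reversal (−8.3% to +10.0%). All three rest on assumed doses, 30% v 25% users and unchanged doses in continuing users. Sign reversal is possible, not expected.

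The consequence is limited. Dose is a secondary outcome, the primary outcome keeps non-users at 0 days, and the dichotomous prescribing analysis captures stopping directly. The trial's main conclusion is not at risk, but the reported dose effect could mislead.

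**What to change.** State in the Analysis section that the dose analysis includes every resident in the prescribing population, with a dose of zero where nothing was dispensed, and keep the linear mixed model as the main analysis. Replace the stand-alone fallback with one of the following:

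- a log-link model that admits zeros, such as Tweedie or quasi-Poisson, with clustering by home (if robust standard errors are used, with a small-sample correction, given about 15 control clusters); or
- a two-part model, binomial for any use and gamma or log-normal for dose among users, whose reported effect is the combined all-resident mean ratio with its confidence interval.

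Show dose among users as descriptive only.

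The cost is a sentence or two of text and slightly more modelling work, with no new data collection. The all-resident mean partly reflects stopping, which the dichotomous outcome also shows, so the two results should be read together.
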